### Interventions

Supplements will be administered as drops from a liquid formulation containing either iron (7.5mg contained in 0.5mL) or its placebo (sorbitol solution USP 70%, an inactive ingredient in the iron supplements). The intervention and placebo will be issued in identical dark brown plastic bottles. The ferrous sulphate (intervention) and sorbitol (placebo) will be manufactured such that they are identical in terms of taste and appearance thus, allowing robust allocation concealment. Infants will be visited in their homes daily for 98 days by the field workers who will administer the drops. Products will be stored at ambient temperature (15–30˚C), away from direct sunlight, at both the MRCG@LSHTM Keneba Field Station main store and Jarra Soma health clinic in a locked room. The procured products have a 12-month shelf-life and expiry dates will be checked by the sub-investigator during study implementation.

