### Follow up

The final study visit will be on Day 99 after 98 days of supplementation. Procedures for blood and faecal collections and storage and anthropomentry will be as per baseline. 

An early termination visit may occur because of a participant’s voluntary withdrawal, trial team decision, or at the discretion of the DSMB. Apart from the safety evaluations, no other evaluations required for the final study visit will be done.

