### Sample size

We intend to enrol 100 infants in the trial, which will be sufficient to have 80% probability that, if the true increase in geometric mean serum iron concentration in the iron group increases by 70% or more relative to the control group, the 95% confidence interval for the ratio would exclude zero (with the additional assumptions that the variance of log
_e_ serum iron concentration [in µmol/L] is 0.76 for each group
^
13
^; 10% of infants in the iron group stop taking iron supplements in the course of the intervention period; and the percentage of infants in the control group who stop taking placebo supplements is negligible) (
Figure 3). In absolute terms, an increase by 70% corresponds to a change of geometric mean serum iron concentration of 3.0µmol/L, assuming that this concentration is 4.3µmol/L in the placebo group (as observed at Day 0 in Armitage
*et al.* 2019
^
1
^), so that it will have increased 7.3µmol/L in the iron group. We consider intervention effects below 3.0 µmol/L (absolute group difference in geometric means) to be unimportant from medical and public health points of view.

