### Statistical analysis

**
*Main study.*
** Statistical analyses will be performed using R studio and STATA software. Intervention groups will be described using conventional summary statistics (e.g., means or counts with standard deviations, medians with 25- and 75-centiles). The primary analysis concerns the effect of intervention on serum iron concentration at Day 99 (i.e., 98 days of intervention with a 1-day wash-out period after administration of the last supplement, assuming that a transient increase in serum iron concentration following iron supplementation will disappear within this period), adjusted for serum iron concentration measured at baseline. Continuous outcomes will be analysed by linear regression, with transformation of the outcome as needed to normalise the distribution of residuals. Analysis will be by modified intention-to-treat, i.e., all infants who were randomised and who received at least one supplemental dose will be included. We also plan to perform per protocol analysis (i.e., to assess the efficacy that can be attained under controlled conditions) to determine the sensitivity of our modified intention-to-treat analysis. To account for missing data, we will use multiple imputations. In secondary analyses, we will adjust for any group imbalances that may occur in prognostic variables measured at baseline. Serum iron concentrations are known to undergo diurnal fluctuation and they are known to be reduced in inflammation
^
18
^. Thus, to account for these effects, we will also conduct secondary analyses with adjustment for the time of blood collection and for plasma concentrations of C-reactive protein and alpha-1 acid glycoprotein at the time of blood collection.

Group differences in adverse events will be analysed using negative binomial regression. In this analysis, we will count adverse events as the number of days with adverse events divided by the total number of days that the infant was observed during the intervention period. In the analysis of diarrhoea, we will count an event if the parent/guardian reported three or more fluid stools (as indicated by a WHO stool chart) in the previous 24-hour recall period
^
19
^. To produce conservative effect estimates, analyses of adverse events will be per protocol.

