### Data and safety monitoring

Field workers will record any adverse events and ensure the safety of participants. Field workers will visit all infants daily during the supplementation period to administer the drops as described above and to check on the infant’s health status. If an infant is found unwell, the study nurse will check on the infant and decide on treatment/referral to the MRCG@LSHTM Keneba health centre in consultation with the Research Clinician. Parents/guardians will complete a weekly questionnaire asking whether they have offered foods or fluids other than breast milk.

The trial will be overseen by a DSMB. Safety data will be reviewed by the DSMB as overall pooled data (open session) and tabulated by coded treatment arm (closed session) at given time intervals. Unblinding of the treatment will only be requested by the DSMB in individual cases if there is a pattern of serious adverse events which may be related to study treatment where the DSMB feels there is ‘potential for harm’. Monitoring the rate of recruitment and level of retention of infants and to examine any trends apparent related to non-retention (e.g., consent withdrawal, loss to follow-up etc.) and to provide advice accordingly.

Recruitment to the trial may be paused upon discretion of the DSMB if any infant has a serious adverse reaction to any of the interventions administered during the trial.

In addition to the DSMB, the Local Safety Monitor will regularly review all adverse events and serious adverse events. This review will focus particularly on adverse events causality and reasons for losses to follow up, raising any concerns or issues that present immediate safety concern with the principal investigators for reporting to the DSMB, while protecting the confidentiality of the trial data and the results of monitoring.

Experimental supplements shall be withheld for seven days following detection of any of the following conditions: confirmed fever (axillary temperature >37.5°C) not associated with teething or vaccination
^
a
^; visually confirmed bloody diarrhea; hospitalization for somatic infection; treatment with antibiotics for any confirmed or suspected somatic infection
^
b
^.

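### Restricting adverse-event comparisons to the per-protocol set is not assured to be conservative: illness can decide who stays in that set, so harm from iron can be understated

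*Protocol article*

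**What the plan says.** All references are to the protocol article.

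- **Statistical analysis, adverse events:** "To produce conservative effect estimates, analyses of adverse events will be per protocol". No between-arm adverse-event analysis in any wider set is described.
- **Statistical analysis, main set:** "Analysis will be by modified intention-to-treat, i.e., all infants who were randomised and who received at least one supplemental dose will be included". Per protocol appears there as a sensitivity analysis with an efficacy purpose: "per protocol analysis (i.e., to assess the efficacy that can be attained under controlled conditions". The article sets no adherence threshold and does not say how withheld doses count.
- **Data and safety monitoring:** "Experimental supplements shall be withheld for seven days following detection of any of the following conditions". The conditions are confirmed fever (teething and vaccination excepted), visually confirmed bloody diarrhoea, admission for infection, and antibiotic treatment for infection.
- **Follow up:** early termination may come from voluntary withdrawal, "trial team decision, or at the discretion of the DSMB".
- **Sample size:** the calculation assumes that "10% of infants in the iron group stop taking iron supplements in the course of the intervention period", with negligible stopping on placebo.

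**The concern.** For a harm outcome, a per-protocol comparison leans towards showing harm only if leaving the set is unrelated to the illnesses being counted. In that case it removes infants with little exposure and reduces dilution. Here the plan links the two. Illness leads to withheld doses and may lead to stopping, and stopping is expected mainly on iron. If the sicker iron infants leave the set more often than the sicker placebo infants, the comparison is no longer the randomised one and it moves towards no harm.

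Safety is a stated objective. The Discussion aims to show benefit without additional adverse effects, and the section on risks and benefits cites the long-standing question of iron and infection and looks ahead to a larger trial. With about 50 infants per arm, a few exclusions can matter.

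**Working it through.** **1. The plan's own figure.** The Sample size section gives 100 infants, variance of log serum iron 0.76, a 70% increase, 80% power and a 95% interval. If 10% of the iron arm stops, the increase is diluted to 0.9 × 70% = 63%, a ratio of 1.63. Then n per arm = 2 × 0.76 × (1.960 + 0.842)² / (ln 1.63)² = 1.52 × 7.85 / 0.2387 ≈ 50, or 100 in total, with power 80.0%. The figure reproduces on this reading, so one-sided stopping is a working assumption of the design. No design figure is given for adverse events.

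**2. Expected stopping by arm.** Allocation is 1:1, so 50 per arm. Iron: 0.10 × 50 = 5. Placebo: about 0.

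**3. Cost of holds.** The plan is 98 daily doses ("Infants will be visited in their homes daily for 98 days by the field workers who will administer the drops"). One hold is 7/98 = 7.1% of doses, two are 14/98 = 14.3%, three are 21/98 = 21.4%. If held doses count as missed, one hold removes an infant at a 95% threshold, two at 90% and three at 80%. At 70%, four holds (28 doses) are tolerated. These thresholds are assumptions.

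**4. Illustrative simulation.** 100,000 infants per arm. Assumptions not in the article:
- gamma frailty with variance 1;
- 4-day illnesses, each triggering a 7-day hold;
- an underlying rate of 1 or 2 episodes per placebo infant;
- an iron effect that acts until the infant stops supplements;
- about 10% stopping in the iron arm only, either at random or following illness.

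Rate ratios of illness days, iron over placebo:

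| True ratio | Episodes | Stopping | All dosed | Per protocol, holds missed, 80% threshold | Per protocol, holds compliant |
|---|---|---|---|---|---|
| 1.5 | 1 | random | 1.44 | 1.19 | 1.46 |
| 1.5 | 1 | after illness | 1.42 | 1.13 | 1.23 |
| 1.5 | 2 | random | 1.39 | 1.11 | 1.41 |
| 1.5 | 2 | after illness | 1.40 | 1.10 | 1.28 |
| 1.0 | 1 | random | 1.00 | 0.99 | 0.99 |
| 1.0 | 1 | after illness | 1.01 | 0.90 | 0.80 |
| 1.0 | 2 | random | 1.01 | 1.00 | 1.01 |
| 1.0 | 2 | after illness | 1.00 | 0.95 | 0.87 |

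With holds counted as missed and a true ratio of 1.5, thresholds from 70% to 95% give 1.05 to 1.30. At 80%, exclusions are 21–24% of iron infants against 9% of placebo infants (1 episode), and 39–42% against 25% (2 episodes). The all-dosed ratio falls a little below 1.5 partly because of stopping and partly because, in the model, an infant already ill cannot start a new illness.

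**5. Reading the table.** There are two separate routes to understatement: counting held doses as missed, and stopping because of illness. The second operates even when holds are compliant. With neither, per protocol is slightly higher than the all-dosed result (1.46 against 1.44; 1.41 against 1.39).

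**The case against.** The best defence is that the hold is ordered by the protocol, so an infant whose drops are withheld is following it and may well remain per protocol. The definition of that set commonly sits in the full protocol or the statistical analysis plan, neither of which is shown. If holds are compliant and stopping is unrelated to illness, per protocol does what its authors probably intended. This stands, and it limits the finding to a property that is not assured.

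A reader might also infer more than the article supports:

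- **That the harmed infants are the ones removed, or that only infants who were never ill remain.** No text says that held doses count against adherence. Even if they did, an infant with two holds (14.3% of doses) stays in at an 80% threshold.
- **That exclusions fall on iron infants only.** The 10% and negligible figures are sample-size assumptions about stopping. They do not forecast per-protocol exclusions, and illness holds would remove placebo infants too.
- **That the simulated sizes apply to this trial.** They rest on assumed rates and thresholds. The model also ties every illness to a hold, whereas the article counts diarrhoea from three fluid stools but holds supplements only for the bloody form. The true overlap is looser.
- **That safety is looked at only per protocol.** The DSMB sees data by coded arm, and a Local Safety Monitor reviews all events. Neither review is described as limited to per protocol, but both are oversight and do not replace the final comparison.
- **That the negative binomial model is misspecified.** The article says "we will count adverse events as the number of days with adverse events divided by the total number of days that the infant was observed". This reads naturally as an incidence rate, which such a model estimates from a count with an exposure offset. It is at most a point to clarify.

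What the defence does not answer is stopping that follows illness. The Follow up section leaves that route open, and the article does not exclude it.

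**Conclusion.** The point holds in limited form. The article fixes between-arm adverse-event analyses to the per-protocol set and justifies this by a direction of bias that its own rules do not secure. Harm from iron can be understated if held doses count as non-adherence, or if infants stop because of illness. If neither applies, there is no understatement.

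The direction under those two conditions is well supported. The size is not known from the document. Under the stated assumptions a true ratio of 1.5 appears as 1.05 to 1.30 by the first route. By the second route alone it appears as 1.23 to 1.28, and a true ratio of 1.0 appears as 0.80 to 0.87, so iron would look falsely protective. The second set of figures also assumes that illness-related stopping occurs in the iron arm only, following the sample-size assumption. Nothing here judges the withholding rule itself.

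**What to change.** In the adverse-event paragraph of Statistical analysis:

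1. Make the main between-arm analysis all randomised infants who received at least one dose, which is the plan's own modified intention-to-treat set. Count every observed day of the intervention period, including days off supplement.
2. Keep per protocol as a sensitivity analysis.
3. State that a hold directed by the protocol does not by itself make an infant non-adherent.
4. Delete the word conservative.

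As an optional clarification, say that the model uses the count of event days with log days observed as an offset.

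The cost is a few sentences and no new data, since infants are already visited daily. The small downside is some dilution from non-adherence, which the retained per-protocol analysis would show.

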**Figure 4. f4:**
[figure not shown]
Acceptability of healthcare interventions: an overview of reviews and development of a theoretical framework (v1).

This coding will be conducted by one researcher and 10–20% will be independently coded by another researcher to cross-check appropriateness of coding. Throughout the coding process, these two researchers will meet regularly to discuss the codes and applicability of the framework and subsequently derived templates for analyses. Any disagreements will be resolved by discussion with a third researcher.

The quantitative data will be summarised and analysed using descriptive statistics to further understand the acceptability of the intervention proposed in the main study. This data will likewise be modelled to the implementation acceptability framework. This quantitative data will help further interpret results from the qualitative data, highlighted triangulated key factors which may have varied the level of acceptability.

### Data and safety monitoring

Field workers will record any adverse events and ensure the safety of participants. Field workers will visit all infants daily during the supplementation period to administer the drops as described above and to check on the infant’s health status. If an infant is found unwell, the study nurse will check on the infant and decide on treatment/referral to the MRCG@LSHTM Keneba health centre in consultation with the Research Clinician. Parents/guardians will complete a weekly questionnaire asking whether they have offered foods or fluids other than breast milk.

The trial will be overseen by a DSMB. Safety data will be reviewed by the DSMB as overall pooled data (open session) and tabulated by coded treatment arm (closed session) at given time intervals. Unblinding of the treatment will only be requested by the DSMB in individual cases if there is a pattern of serious adverse events which may be related to study treatment where the DSMB feels there is ‘potential for harm’. Monitoring the rate of recruitment and level of retention of infants and to examine any trends apparent related to non-retention (e.g., consent withdrawal, loss to follow-up etc.) and to provide advice accordingly.

Recruitment to the trial may be paused upon discretion of the DSMB if any infant has a serious adverse reaction to any of the interventions administered during the trial.

In addition to the DSMB, the Local Safety Monitor will regularly review all adverse events and serious adverse events. This review will focus particularly on adverse events causality and reasons for losses to follow up, raising any concerns or issues that present immediate safety concern with the principal investigators for reporting to the DSMB, while protecting the confidentiality of the trial data and the results of monitoring.

Experimental supplements shall be withheld for seven days following detection of any of the following conditions: confirmed fever (axillary temperature >37.5°C) not associated with teething or vaccination
^
a
^; visually confirmed bloody diarrhea; hospitalization for somatic infection; treatment with antibiotics for any confirmed or suspected somatic infection
^
b
^.

### Withdrawal of participants

In case the participant decides to withdraw participation or consent during the study, we will not work on the participant’s samples without permission, but any information already generated from the samples until the time of withdrawal will be used and samples already collected, for which they have given consent, will also be analysed and data used. The study clinician may also ask for tests for the participant’s safety. The principal investigator/sub-investigator will ask about the reason for any withdrawal and follow-up with the participant regarding any unresolved adverse events.

### Participant confidentiality

Any identifiable data collected will be stored securely and their confidentiality protected in accordance with the UK General Data Protection Regulation (UK GDPR) and the Data Protection Act (2018). Participant confidentiality, privacy and anonymity will always be ensured. All data will be anonymised, and individuals will not be identifiable.

### Future use of stored specimens and data

Aliquots of blood and faecal samples will be kept frozen at -80°C for future analysis. This may include export of samples. We will obtain informed consent from the parents/guardians for this within informed consent. The blood and faecal samples collected during the trial may be used to support other research in the future, and may be shared anonymously with other researchers, for their ethically approved projects. Any future use of data or samples will require approvals from the principal investigator, MRCG@LSHTM Scientific Coordinating Committee, and Ethics Committee.

## Ethics

These studies will be conducted in accordance with the principles set forth in the ICH Harmonised Tripartite Guideline for Good Clinical Practice and the Declaration of Helsinki in its current version whichever affords the greater protection to the participants. The studies have been reviewed by the MRCG@LSHTM Scientific Coordinating Committee, The Gambian Government/MRC Unit The Gambia Joint Ethics Committee and the Ethics Committee at LSHTM (Approval IDs: 19092; 21257). All amendments will go through the same process and the changes will be communicated with investigators, trial participants, trial registries, journals, and regulators.

## Dissemination and data access

All key findings from this study will be submitted for publication in peer-reviewed journals. Our planned dissemination avenues include at least three publications in high impact peer-reviewed open-access scientific journals with a wide readership, presentation at international conferences (e.g., the Micronutrient Forum) and dissemination of the trial findings to international and Gambian organizations.

Any request for use of study data will go through approval from the Sponsor and the Ethics Committee. All data will be in an anonymous format for external users. Data sharing will agree with the Sponsor policy on research data sharing.

## Study status

The pilot study has recruited all 100 infants (November 2021) with the final infant due for follow up in March 2022. The qualitative study focus group discussions have been completed, with the interviews commencing in late December 2021.

## Discussion and conclusion

In infants under six months of age, with normal birth weight, exclusive breastfeeding and delayed cord clamping are the only practices recommended to prevent anaemia by the WHO guidelines
^
23
^. For low-birth-weight infants, WHO guidelines recommend an external source of iron before six months of age. Maternal iron status is important during pregnancy as iron stores for the first few months of life are passed from mother to infant in utero
^
24
^. The iron received in utero is used for growth and development in the first six months of life, acting as a buffer for the nutritional needs of new tissue. Randomised trials have shown that antenatal iron supplementation and delayed cord clamping each increase iron stores in neonates
^
25
^.

This study aims to determine if early supplementation of infants with iron will improve serum iron concentrations without additional adverse effects and without undermining exclusive breastfeeding. This is the first time such an intervention will be done in this age group for this population. Further, the planned mixed methods research will explore the effects of this clinical intervention on relevant outcomes while observing and gathering information on implementation. The use of qualitative and quantitative methods will shed light on acceptability of iron supplementation in young infants through the perspective of local stakeholders and mothers as the primary caregivers.

